## Potential Risks and Benefits

### Potential Risks

The subject may experience a brief moment of physical discomfort or pain during the finger prick procedure and the venipuncture and there is a possibility of bruising and/or infection at the site of the finger-prick or venipuncture.

Subjects may experience ‘transient bitter taste’ as a possible side effect from the study drug. Artesunate is generally very well tolerated but may occasionally cause mild abdominal symptoms and dizziness and changes in the laboratory and EKG parameters. While still well below the total dose that has caused significant side effects in animal safety testing, the 6 mg/Kg artesunate dose regimen is an experimental dose that has not been previously administered to humans. It is therefore not possible to rule out the possibility of toxicity or adverse effects at this dose. A Safety Monitoring Committee will be convened prior to study execution and will monitor closely the AE profiles of artesunate-treated patients with special emphasis on the 6 mg/kg cohort.

There is a risk that malaria may recur. All subjects will therefore be closely monitored and quickly treated should any signs or symptoms of malaria be detected.

### Potential Benefits

As subjects will be hospitalized for at least the first 7 days and then closely monitored for any signs and symptoms of malaria, they will have the benefit of close medical supervision. All doses of the study drugs will be administered under direct supervision by medical/nursing staff trained in drug administration, and any change in the course of their infection or any adverse experiences will be recognized and treated more rapidly than would normally occur if they were treated as outpatients in a government facility.

Subjects will be immediately treated for any reappearance of parasitemia that occurs. Subjects who fail initial therapy, based on parasitological parameters, will be treated with a standard regimen following the national treatment guideline that is known to be effective. In addition, while admitted to the hospital the subjects may be examined and treated for other concurrent illnesses. Subjects will also receive medical attention and appropriate standard medical care or referral should they become ill during the study.

An early detection of artemisinin resistance and the knowledge whether failures can be overcome by increasing the dosage of artemisinins will directly benefit the malaria control program and the population of Cambodia and will allow for adequate countermeasures to be taken to avert a global disaster. The National Malaria Program of Cambodia will benefit from human resource capacity building, access to modern laboratory methodology (particularly novel techniques for *in vitro* drug sensitivity testing of antimalarial drugs) and GCP training for government staff.

# Objectives

**3.1 PRIMARY OBJECTIVE:**

- The principal aim of this project is to determine the role of varying doses of artesunate for treatment outcome and whether higher doses of artesunate could overcome the problem of reduced artemisinin sensitivity in the region.
- To determine the safety and tolerability of this previously untested experimental high dose (6 mg/Kg/D X 7 day, total 42 mg/Kg) artesunate monotherapy regimen.

**3.2 SECONDARY OBJECTIVES:**

- Validate treatment response parameters (PCT, FCT, GCT, and the proportion of patients parasitemic on Day 3) for their role in predicting failures.
- To further evaluate the current malaria *in vitro* drug sensitivity situation along the Cambodian-Thai border.
- To validate potential genetic markers of artemisinin resistance and the role of identification of low level parasitemia by PCR

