### Primary Outcome Measures (Clinical Outcomes)

PCR-corrected clinical outcome will be assessed for Day 28 and 42.

Classification of clinical outcomes:

- **Adequate Clinical and Parasitological Response (ACPR)**

• Absence of parasitemia on Day 28 and 42 irrespective of temperature without previously meeting any of the criteria of Early Treatment Failure or Late Clinical Failure or Late Parasitological Failure.

- **Early Treatment Failure (ETF)**

• Development of danger signs (e.g. impaired consciousness, convulsions, respiratory distress) or severe malaria on Day 1, Day 2 or Day 3, in the presence of parasitemia

• Parasitemia on Day 2 higher than Day 0 count irrespective of temperature

• Parasitemia on Day 3 with temperature ≥ 37.5 °C

• Parasitemia on Day 3 ≥ 25 % of count on Day 0.

- **Late Treatment Failure (LTF)**
  - Late Clinical Failure (LCF)

• Development of danger signs or severe malaria after Day 3 in the presence of parasitemia, without previously meeting any of the criteria of Early Treatment Failure

• Presence of parasitemia and temperature ≥ 37.5 °C (or history of fever) on any day from Day 4 to Day 28/42 without previously meeting any of the criteria of Early Treatment Failure

- - Late Parasitological Failure (LPF)

• Presence of parasitemia on any day from Day 7 to Day 42 and temperature < 37.5 °C, without previously meeting any of the criteria of Early Treatment Failure or Late Clinical Failure

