## Sample Size Considerations

Enrollment target for arms 1 and 3 will be 60 evaluable subjects (those completing study endpoints). Arm 2 will be used as a comparator for the 4 mg/kg study cohort tested in the study conducted in 2006. Subjects will be enrolled in the 3 groups at a ratio of 2:1:2. The dropout rate is expected to be approximately 25%. Any dropouts (e.g. withdrawals, lost-to-follow-ups etc.) will be replaced in the same arm. Therefore 190 persons may be enrolled to achieve 150 evaluable subjects. In case the enrollment target of 150 evaluable subjects cannot be met within the approved study duration an application for extension of the study duration will be filed.

Arm 2 serves as a control and will serve as a bridge to the study performed in 2006/2007. The sample size in this arm is lower as results from 60 evaluable patients are available from the earlier study conducted at the same site.

The sample size for detecting a significant difference between the 2 study arms by uncorrected Chi2-test is calculated based on an expected cure rate (i.e. early and late treatment failures) of 80% in arm 1 and 95 % in arm 3:

α 0.1

1 – β 0.8

p0 0.8

p1 0.95

Calculated sample size per arm 59

With 60 patients in arm 1 and 60 patients in arm 3 there will be a >80% chance of detecting a significant difference by uncorrected Chi2-test at a two sided 0.1 significance level. This assumes that the response rate in arm 1 is 0.8 and the response rate in arm 3 is 0.95.

Figure 1: Case sample size relative to power for α = 0.1 (Dupont and Plummer 1997)

[figure not shown]

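### The failures against which Day-3 parasitemia, PCT and FCT are to be validated partly consist of those same markers, so predictive accuracy can be overstated

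*Protocol*

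**What the plan says.** Section 3.2 (Secondary Objectives) sets out to "Validate treatment response parameters (PCT, FCT, GCT, and the proportion of patients parasitemic on Day 3) for their role in predicting failures". It does not limit the target to late failure, recrudescence or events after clearance.

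The section on primary clinical outcome measures defines failure. Two early treatment failure (ETF) criteria use the Day-3 smear: "Parasitemia on Day 3 with temperature ≥ 37.5 °C" and "Parasitemia on Day 3 ≥ 25 % of count on Day 0". The second needs no fever. Late clinical failure (LCF) includes "Presence of parasitemia and temperature ≥ 37.5 °C (or history of fever) on any day from Day 4 to Day 28/42". Late parasitological failure (LPF) is "Presence of parasitemia on any day from Day 7 to Day 42 and temperature < 37.5 °C". Both late categories apply only to patients who have not already met an ETF criterion. The sample size section describes its outcome as the "expected cure rate (i.e. early and late treatment failures", so early and late failures are pooled there.

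Under Study Procedures, inpatient smears are taken every 6 hours until two successive ones are negative. The next scheduled smear is on Day 14. Under Secondary Outcome Measures, the clearance times run to the first of a series of negative tests, and fever clearance requires 48 hours below 37.5 °C. The statistical section gives between-arm tests for the clearance times but no method for the prediction objective.

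**The concern.** The objective asks whether a slow early response foretells later return of parasites. It follows from ARC1, where PCT was 97.6 hours in the four patients whose parasites re-emerged and 52.2 hours in those cured. A patient who is a failure because the Day-3 smear was positive, or because parasites persisted on Days 4 to 7, cannot help to answer that question. In such a patient the marker does not precede the outcome; it is the outcome. Counting these patients among the failures credits the marker with detections it could not have missed, and a marker with no prognostic value could then appear useful. That matters because Day-3 positivity and PCT are candidate early indicators of artemisinin resistance.

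**Working it through.** **Step 1. Which criteria fix the marker?**

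| Route to failure | Day-3 smear positive by definition? | PCT long by definition? | FCT long by definition? |
|---|---|---|---|
| ETF: Day-3 parasitemia with temperature ≥ 37.5 °C | Yes | Yes | Largely (fever still present on Day 3) |
| ETF: Day-3 count ≥ 25% of Day 0 | Yes | Yes | No |
| LCF on Days 4–6, never cleared | Yes | Yes, over 96 h | Only if fever is measured; not by history alone |
| LPF on Day 7, never cleared | Yes | Yes | No |
| LCF or LPF after clearance | No | No | No |

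Because routine smears stop after two negatives, a positive smear on Days 4 to 7 comes mainly from a patient who has not cleared. The remaining ETF criteria (danger signs on Days 1–3, or a Day-2 count above Day 0) do not fix the Day-3 smear. GCT enters no criterion. PCR correction does not remove the overlap, since parasites that never cleared would be expected to match the Day-0 genotype.

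**Step 2. The plan's own figures.** The protocol gives no figure for the prediction objective. The figures used below as inputs are consistent. In ARC1, 56/60 = 93.3%, and its exact 95% interval recomputes to 83.8–98.2% as stated. For 80% versus 95% cure at two-sided alpha 0.1, the required size recomputes to 60 per arm (59 stated), with power 0.806 at 60 per arm.

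**Step 3. Illustration in arm 1.** Inputs:
- Failures: 60 × (1 − 0.80) = 12, from the sample size assumption.
- Day-3 positivity: 22%, from ARC1.
- Assumption: the marker carries no information, so 22% are positive both among the cured and among failures not fixed by the marker.
- k: failures that are marker-positive by definition. The documents do not give k, so a range is shown.

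Apparent sensitivity = (k + 0.22 × (12 − k)) / 12. Apparent positive likelihood ratio = sensitivity / 0.22.

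| k | Sensitivity | Likelihood ratio |
|---|---|---|
| 0 | 2.64/12 = 22% | 1.0 |
| 1 | 3.42/12 = 28.5% | 1.3 |
| 2 | 4.20/12 = 35% | 1.6 |
| 4 | 5.76/12 = 48% | 2.2 |
| 6 | 7.32/12 = 61% | 2.8 |

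**Step 4. All three arms.** Assume cure of 80%, 93.3% (the ARC1 rate, for arm 2) and 95%. Failures are then 12 + 2 + 3 = 17 of 150, and Day-3 positives are 0.22 × 150 = 33. For an uninformative marker, sensitivity = (k + 0.22 × (17 − k)) / 17, which is 22%, 27%, 36%, 45% and 59% at k = 0, 1, 3, 5 and 8. The positive predictive value, with the same numerator over 33, is 11%, 14%, 18%, 23% and 30%. If true sensitivity for the other failures is 50%, apparent sensitivity is 50%, 53%, 59%, 65% and 74%.

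**Step 5. Direction.** Each such failure adds one to both the numerator and the denominator of sensitivity, so the shift is zero or upward.

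**The case against.** The strongest reply is that ARC1, at the same site, showed none of this. There 22% were parasitemic at 72 hours (about 13 of 60), yet all four failures were re-emergence (3 LPF, 1 LCF), so at least about 9 Day-3 positives were cured. Zero of 60 has an exact upper 95% limit of about 6.0%, or 3.6 patients in an arm of 60, so k = 4 and k = 6 lie above what ARC1 supports. This stands as a limit on the size. It does not settle k for arm 1, which receives half the ARC1 daily dose and is planned at 20% failure against ARC1's 6.7%. One ARC1 failure also had a PCT of 133 hours, so persistence beyond Day 4 does occur.

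Second, the protocol specifies no sensitivity or predictive value, and an analysis plan that is not shown could restrict the outcome. That is fair as to method. But the objective names failures as its target and the protocol defines failure, so the overlap is in the text and is more than a detail left open.

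Third, restricting the analysis to patients who cleared conditions on a post-baseline event and drops the slowest responders. That is a real cost, and it is why those patients should still be reported.

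A reader might also infer that the validation is wholly circular and is bound to overstate accuracy. The documents do not support that. Day-3 parasitemia without fever and below 25% of baseline is not a failure. Afebrile parasitemia counts only from Day 7. A long FCT meets no criterion by itself. With no definitional failures there is no inflation.

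**Conclusion.** The concern holds in a limited form. As the terms are defined, Day-3 parasitemia and PCT, and to a lesser extent FCT, are validated against an outcome that they partly constitute. Accuracy for these markers can be overstated, and cannot be understated by this route. The inflation is nil if every failure is a recurrence after clearance, as in ARC1. For an uninformative marker in arm 1 it is about 6 percentage points of sensitivity with one definitional failure and 13 points with two. The 26 and 39 points at k = 4 and k = 6 show how the bias grows; they are not forecasts. These sizes rest on 12 failures, 22% positivity and an assumed k. GCT, the primary ACPR comparison and the sample size are not affected. This is an inexpensive improvement to one secondary objective.

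**What to change.** For this objective only, define the outcome as PCR-confirmed *P. falciparum* recrudescence after initial clearance, meaning parasites that reappear after two successive negative smears, up to the Day 42 visit. Analyse it among patients who cleared and had not already failed. Report early failures and never-cleared failures separately with their marker values, and add a sensitivity analysis on all failures so that the effect of the definition can be seen. Leave the primary ACPR definition unchanged.

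This needs wording in the protocol or the analysis plan and no new data. The costs are fewer events, wider intervals for predictor accuracy, and conclusions limited to patients who cleared.

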# Study Design

This is an open label, randomized study. The study design is largely based on the WHO recommendations for the ‘Assessment and Monitoring of Antimalarial Drug Efficacy for the Treatment of Uncomplicated Falciparum Malaria’ (WHO, 2003). Patients with acute uncomplicated falciparum malaria will be randomly enrolled in 3 arms: All patients in arm 1, 2, and 3 will receive artesunate monotherapy for 7 days (Table 7). The ratio of enrollment into the 3 groups will be 2:1:2. Arm 2 serves as a control and will serve as a bridge to the ARC 1 study performed in 2006/2007. Patients in Arm 1 will receive a relatively low “standard” dose, and patients in Arm 2 will receive the intermediate dose of 4 mg/kg that was used in the ARC1 study. Patients in Arm 3 will receive an experimental “high-dose” regimen. Currently available safety data extends to subjects who have received the 28 mg/Kg total dose over 7 days and to another study administering 8 mg/Kg/day for 3 days (total dose 24 mg/Kg). Subjects randomized into this study’s ‘high-dose’ Arm 3 will, therefore, receive a total dose that is higher than has been previously studied in humans.

Table 7: Artesunate dosing for treatment groups 1-3.

| Treatment Group | Sample Size | Artesunate | |
| --- | --- | --- | --- |
| Dosing  mg/kg/day x 7 days | Total Dose/kg |
| 1 (Artesunate, “standard” dose) | 60 | 2 | 14 |
| 2 (Artesunate, ARC1 dose) | 30 | 4 | 28 |
| 3 (Artesunate, experimental “high” dose) | 60 | 6 | 42 |

Patients will be admitted to the hospital to receive directly observed therapy and close safety monitoring for the duration of study drug administration (7 days) or until all signs and symptoms of malaria have disappeared, whichever is longer. Thereafter patients will regularly report for follow-up (at least on Days 14, 21, 28, 35, and 42). Blood will be drawn on the day of admission (before initiating therapy) for *in vitro* drug sensitivity testing and for PCR (markers of drug resistance and to distinguish recrudescence from reinfection by genotyping). Malaria smears will be prepared up to 8 times on Day 0, and then up to 4 times a day thereafter until parasite clearance, and on Days 14, 21, 28, 35, and 42 or whenever symptoms consistent with malaria appear. Plasma samples for determining anti-malarial drug levels will be obtained on Days 0 and 6. Over the entire study, up to approximately 59 ml of blood may be drawn by venipuncture from patients who do not fail treatment. An additional approximately 26 ml of blood will be drawn in case of treatment failure. The study duration for each individual patient will be 42 days.

All patients in group 1, 2, and 3 will receive artesunate monotherapy for 7 days for the treatment of their *P. falciparum* infection. Patients who develop early treatment failures, who fail to completely clear parasites by the end of the 7th day or who have a recurrence of parasitemia any time until Day 42 will be treated with 1st or 2nd line therapy following the national treatment guidelines of Cambodia.

**Study drug:**

Artesunate

| Chemical name: | Artesunate has the chemical name (3R,5aS,6R,8aS,9R,10S,12R,12aR)-Decahydro-3,6,9-trimethyl-3,12-epoxy-12H-pyrano[4,3-j]1,2-benzodioxepin-10-ol,hydrogen succinate |
| --- | --- |
| Generic name: | Artesunate |
| Trade name: | Artesunate |
| Dosage form: | Tablet |
| Strength: | 50 mg |
| Batch/lot number | 071201 |
| Manufactory date and expiry date | Mfg. date: 07/12/2007  Exp.date: 12/2010 |
| Manufacturer: | Guilin Pharmaceutical Co,. Ltd.  Add: [name]  Post code: 541002  [contact]  [contact]  [http://www.guilinpharma.com](http://www.guilinpharma.com/) |
| Quality: | WHO pre-qualify http://www.guilinpharma.com/english/magazine/Empolder_list.asp?Action=0&id=192 |
| Source: | Supplied by the World Health Organization |

# Study Population

## Selection of the Study Population

Subjects will be male and non-pregnant female patients (age 18 - 65 years), recruited by active or routine passive case detection at Tasanh Health Center and other health centers in Battambang Province, Cambodia, who present with acute uncomplicated falciparum (Pf) malaria. Uncomplicated falciparum malaria is defined as falciparum malaria in the absence of applicable available signs or symptoms consistent with severe malaria as defined by WHO (WHO 2000). Eighteen years is the age at which individuals in Cambodia can start to provide their own consent. No additional recruitment material will be used in patient recruitment. As part of the Cambodian malaria control program malaria cases are routinely detected by active case detection (i.e. teams that collect diagnostic blood smears in the field) and referred to the nearest treatment facility. Subjects diagnosed with uncomplicated Pf malaria upon evaluation will be verbally notified about the ongoing trial, and asked to participate if interested. Study personnel will screen all persons reporting that they want to take part in the study, give study information and informed consent to the subject and screen for inclusion/exclusion criteria. The patients will be given the choice of either receiving standard of care treatment (artemisinin-based combination therapy) for their malaria or participating in the study. If potential volunteers cannot read the consent form, study personnel will verbally review the study information/consent form with them and answer all questions.

## Study Site

The study will be performed in Battambang Province, Cambodia. In-patient care will be provided at Tasanh Health Center under direct supervision of the investigators. The local personnel are trained and have experience in recruiting and providing in-patient care to study subjects.

## Inclusion Criteria

Male and female subjects with a diagnosis of acute falciparum malaria meeting all criteria listed below may be included in the study:

1. Acute symptomatic falciparum malaria infection as determined by malaria smear with a parasite density of 1000 to 200,000 asexual parasites/L as determined on the thick/thin screening smear with fever (defined as ≥37.5ºC), or reported history of fever within the last 48 hours.
2. Age: 18-65 years old
3. All females between the age of 18 and 50 are required to have a negative human chorionic gonadotropin (hCG) pregnancy test (urine). All females of childbearing potential (not surgically sterile, or less than two years menopausal) are required to use an acceptable method of contraception, such as implant, injectable, or oral contraceptive(s), if possible with additional barrier contraception, intrauterine device, sexual abstinence, or vasectomized partner, throughout the study.
4. Written informed consent obtained
5. Willing to stay under close medical supervision for the study duration of 42 days
6. Otherwise healthy Out-patients

## Exclusion Criteria

Subjects presenting with any of the following will not be included in the study:

1. Pregnant women, nursing mothers, or women of childbearing potential who do not use an acceptable method of contraception (as described in Inclusion Criteria, #3)
2. Mixed malaria infection on admission by malaria smear
3. A previous history of intolerance or hypersensitivity to the study drug artesunate or to drugs with similar chemical structures, such as artemether, artemisinin or dihydroartemisinin
4. History of malaria drug therapy administered in the past 30 days
5. Previous participation in this trial, or participation in any other studies involving investigational or marketed products, concomitantly or within 30 days prior to entry in the study
6. History of significant cardiovascular, liver or renal functional abnormality or any other clinically significant illness, which in the opinion of the investigator would place them at increased risk.
7. Symptoms of severe vomiting (no food or inability to take food during the previous 8 hours).
8. Signs or symptoms of severe malaria (adapted from WHO recommendations (2003): prostration, impaired consciousness, respiratory distress, convulsions, systolic blood pressure < 70 mm Hg, abnormal bleeding, severe anemia with hemoglobin <8 g/dL or HCT <24%, hyperparasitemia at >4% parasitized red blood cells).
9. Unable and/or unlikely to comprehend and/or follow the protocol

## Randomization Procedures

Subjects will be assigned unique identification codes (ARC08 followed by a 3 digit number) in order of inclusion and randomly assigned to either one of the artesunate groups. The ratio of enrollment into the three groups is 2:1:2. Randomization will not be stratified and will be done using random number tables in blocks of 10. A randomization list will be created prior to beginning the trial. Sealed individual envelopes that will be opened only on enrollment of each subject will be used. The study personnel enrolling the subject will therefore not know which group the patient will be assigned to until opening the envelope.

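### A single published block size of 10 in an open-label trial makes some allocations deducible, so the protocol's concealment statement does not hold for every patient

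*Protocol*

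**What the plan says.** Section 5.5 (Randomization Procedures) sets the ratio, "The ratio of enrollment into the three groups is 2:1:2", and states that "Randomization will not be stratified" and that it "will be done using random number tables in blocks of 10". A list is made before the trial starts. On delivery it says "Sealed individual envelopes that will be opened only on enrollment of each subject will be used". It then draws a conclusion: "The study personnel enrolling the subject will therefore not know which group the patient will be assigned to until opening the envelope".

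Section 4 (Study Design) says "This is an open label, randomized study". Section 5.2 (Study Site) adds "In-patient care will be provided at Tasanh Health Center under direct supervision of the investigators". Section 5.1 allows recruitment at other health centers in the province as well, but no second list or stratum is described.

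The text does not call the block size fixed. A single size of 10 is the plain reading, and nothing says that it is withheld from the site.

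**The concern.** Sealed envelopes stop staff from reading the next assignment. They do not stop staff from deducing it. At 2:1:2 a block of 10 holds four Arm 1, two Arm 2 and four Arm 3 places. With the size printed in the protocol, one running list and open treatment, nine visible allocations give away the tenth. The concluding sentence of Section 5.5 therefore does not follow from the procedure before it.

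What is at stake is selection at entry. Arm 3 is the experimental dose, which the protocol presents as untested and places under special safety review, so staff could have a view on who should receive it. Some entry decisions are discretionary: one exclusion covers illness "which in the opinion of the investigator would place them at increased risk", and another turns on whether the patient is likely to follow the protocol. The primary analysis in Section 11.1 is a chi-square test of cure in Arm 1 against Arm 3, with no covariate adjustment stated there. Selective entry into either arm would bias that contrast. The blinded microscopy in Section 6.2.3 protects smear reading, not who enters which arm.

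**Working it through.** The protocol gives no figure for predictability, so there is none to reproduce.

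**Inputs.** Block of 10 at 2:1:2, so 4/2/4 (Section 5.5); past allocations visible (open label, Section 4); target of 150 evaluable subjects, or 150/10 = 15 blocks (Section 11.2). Assumption: the observer knows the block size and has seen every allocation so far.

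**Allocations that are fully certain.** An allocation is certain when only one arm has places left, that is, when it lies in the closing run of a single arm. The expected length of that run is the sum over k of the probability that the last k places are all the same arm:
- k = 1: 1 (the tenth place is always certain)
- k = 2: (4×3 + 2×1 + 4×3)/90 = 26/90 = 0.289
- k = 3: 2×(4×3×2)/720 = 48/720 = 0.067
- k = 4: 2×(4×3×2×1)/5040 = 48/5040 = 0.0095

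The sum is 1.365 per block of 10. Over 15 blocks, 15 × 1.365 = 20.5 of 150. Places one to nine contribute only 0.365 per block: the ninth is certain in 28.9% of blocks and the eighth in 6.7%.

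**Whether the next patient is in Arm 3.**
- Certain to be Arm 3 (only Arm 3 places left): 4/10 + 12/90 + 24/720 + 24/5040 = 0.400 + 0.133 + 0.033 + 0.005 = 0.57 per block.
- Certain not to be Arm 3 (all four Arm 3 places used): 6/10 + 30/90 + 120/720 + 360/5040 + 720/30240 + 720/151200 = 0.600 + 0.333 + 0.167 + 0.071 + 0.024 + 0.005 = 1.20 per block.
- Total: 0.57 + 1.20 = 1.77 per block.

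**Best guess.** The observer always names the arm with most places left. With n = a + b + c places left, the expected number of correct guesses is G(a,b,c) = max(a,b,c)/n + (a/n)G(a−1,b,c) + (b/n)G(a,b−1,c) + (c/n)G(a,b,c−1), with G(0,0,0) = 0. This gives G(4,2,4) = 5.59 of 10, or 56%. Without block knowledge, always naming Arm 1 or always naming Arm 3 is right 40% of the time. Over 150 allocations that is about 84 correct against 60.

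**Effect of varying the block size.** In 400 simulated trials of 150 patients, blocks were drawn at random from 5, 10 and 15. The observer knew that set of sizes but not the order.

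| Design | Certain allocations per 150 | Best-guess success |
| --- | --- | --- |
| Blocks of 10 only | about 20.5 | about 56% |
| Mixed 5, 10 and 15, set known | about 4.5 | about 55% |

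Varying the size removes most of the certainty and almost none of the guessing advantage while the set of sizes is known. By the same recursion, a known block of 5 used alone would be worse than the present design: 24% certain and 61% guessable.

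**The case against.** Block randomization with sealed envelopes is conventional, and 10 is already twice the smallest block that keeps 2:1:2. Harm needs three things: staff who know the size, who keep a running count, and who act on it. The protocol reports none of these.

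It also limits the room to act. Severe malaria, hyperparasitaemia and severe anaemia are excluded outright, and parasite density is capped at entry. Patients are acutely ill and may choose standard treatment instead, so holding one back for a preferred envelope would be difficult. Identification codes follow the order of inclusion.

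These points stand as limits on the likely harm, although the two judgement-based exclusions still leave some discretion. They do not rescue the concealment sentence, which is a claim about what staff can know.

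A reader might go further in three ways that the documents do not support:
- **That staff can often foresee places before the tenth.** They seldom can: 0.365 of the first nine per block, about 4%.
- **That the rate can be scaled to all 190 possible enrolments.** Section 11.2 replaces dropouts in the same arm without saying how. Enrolments beyond 150 need not follow intact 4/2/4 blocks and could be more or less predictable.
- **That a single center enrols every patient.** Section 5.2 places in-patient care at one center, but Section 5.1 recruits more widely.

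**Conclusion.** The point holds, at low severity. The statement in Section 5.5 that enrolling staff cannot know the arm before opening the envelope is not true for every patient under the stated procedure. The figures assume that the observer knows the size of 10 and has tracked every allocation, and that the list is followed in intact blocks. On that footing about 20 of 150 allocations are certain beforehand, and a best guess is right 56% of the time rather than 40%.

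A reader might infer that selection bias is present or expected. The documents do not support that: they make tracking possible but do not show that it occurs. The size and direction of any bias in the Arm 1 versus Arm 3 comparison cannot be derived from them. The reason to act is that the weakness is cheap to remove before enrolment and cannot be repaired afterwards.

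**What to change.** Before enrolment, generate the list with randomly varied block sizes that are multiples of 5 (for example 5, 10 and 15), which keeps 2:1:2. Record the sizes in a restricted document held away from the site. Amend Section 5.5 to say only that permuted blocks of varying, undisclosed size are used, and limit its closing sentence to what the envelopes achieve. Both parts are needed: varying the size cuts certain allocations to about 4.5 per 150, but best-guess success stays near 55% if the set of sizes is known. The gain in guessing from full secrecy was not calculated. The same amendment could state how same-arm replacements are drawn, since replacements made outside the list would be known in advance.

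The cost is a new list and a small protocol amendment, which Section 14.2 sends to all the reviewing ethics boards. Possible imbalance is slightly larger if enrolment stops mid-block. Sample size, procedures and treatment do not change.
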